### 6.6. Adverse Events

As the trial does not involve any new treatment protocols other than the routine standard care protocols, no serious adverse events are expected. However, all participants will receive information on whom to contact in case of a clinical emergency.

Any potential serious adverse events are likely to be limited to the embryos and may include:Failure of embryos to survive biopsy procedure.Physical integrity of the biopsy samples being compromised in transit.

### 6.7. Statistical Considerations

#### Sample Size

For this pilot feasibility randomised controlled trial, a sample size of 100 women was determined. Patients will be recruited to the study at their initial consultation at the fertility clinic, and further recruitment will continue through their monitoring scans until the day of egg collection. Additional centres may be involved in the full study if it goes ahead. This sample size allows us to estimate recruitment rates with a margin of error of ±10.5% around the true rate, providing an 80% confidence interval. While formal hypothesis testing is not the primary focus of this pilot study, an alpha value of 0.05 (5%) and a beta value corresponding to 80% power (β = 0.2) would be considered standard if a preliminary hypothesis testing were conducted [26]. Given the strict regulatory framework governing IVF in the UK, particularly the mandatory reporting of all IVF treatment outcomes, as required by the Human Fertilisation and Embryology Authority (HFEA), we anticipate nearly complete follow-up, approaching 100%.

### 6.8. Statistical Analysis

As this is a pilot study, the main emphasis will be on the acceptability of the intervention and the randomisation process to couples, and on adherence to the protocol. However, following the “All Trials” principle, we will also present a full analysis appropriate for a randomised controlled trial [27].

Baseline comparisons will be made of female age, previous live birth, cause of infertility, number of previous IVF attempts by the woman, ovarian reserve (assessed by the total antral follicle count: 7 or less; 8–20; more than 20), type of ovarian stimulation protocol (gonadotrophin releasing hormone (GnRH) agonist or GnRH antagonist; human chorionic gonadotrophin (hCG) or GnRH agonist trigger), and standard IVF or ICSI. The results will be presented as percentages or mean (SD), as appropriate.

### 6.9. Interim Data Analysis and Data Monitoring

#### Recruitment Progress

The target of recruiting 60 women out of 100 within 18 months was set as a feasibility threshold. If at least 60 out of 100 participants are recruited within the 18-month period, the study will be deemed to have met the recruitment feasibility threshold, and the study will proceed to the main phase. The investigation will stop without proceeding to the main study if the pilot fails to show adequate recruitment after 18 months. If this target is not met, it will prompt a reassessment of the recruitment strategies to ensure the viability of progressing to a larger-scale study.

If the sample size is insufficient, the protocol will incorporate supplementary analyses, such as Bayesian methods, to provide more nuanced insights with limited data. Statistical tests for primary and secondary outcomes will be specified, with methods like logistic regression or survival analysis used as appropriate. To address the need for multiple comparisons, the protocol will apply correction techniques, such as Bonferroni adjustment or false discovery rate control, to ensure statistical rigour and minimise Type I errors.

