## 4. Primary End Point

Our primary outcome of interest will be the ability to recruit, randomise, and ensure adherence to the study protocol to plan the full study.

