### 6.2. Timing of Randomisation

Randomisation will occur on day 3 following egg collection. At this point, all consented patients will be evaluated for eligibility. Specifically, patients will be randomised if they have at least three good-quality embryos, as assessed using the embryo-scoring system of the Association of Clinical Embryologists (UK).

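### The pilot's progression rule prescribes two incompatible actions if the 60-in-18-months target is missed, and does not say whether the 60 are women recruited or women randomised

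*Protocol article*

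**What the plan says.** Section 6.9, under Recruitment Progress, sets the threshold: "The target of recruiting 60 women out of 100 within 18 months was set as a feasibility threshold". If it is met ("If at least 60 out of 100 participants are recruited within the 18-month period"), the recruitment threshold counts as satisfied and the study goes on to its main phase. That sentence attaches no further condition.

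Two consecutive sentences then deal with a miss. The first: "The investigation will stop without proceeding to the main study if the pilot fails to show adequate recruitment after 18 months". The second: "If this target is not met, it will prompt a reassessment of the recruitment strategies", the stated aim being to keep a larger trial viable.

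Other sections bear on what is being counted:

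- Section 6.7 (Sample Size): "Patients will be recruited to the study at their initial consultation at the fertility clinic". Sections 6.7 and 2.6 both let recruitment run on through the monitoring scans, ending on the day of egg collection.
- Section 6.2: randomisation is on day 3 after egg collection, when consented women are checked, and "patients will be randomised if they have at least three good-quality embryos".
- Abstract: the pilot aims to randomise 100 patients.
- Section 4: the primary outcome is "the ability to recruit, randomise, and ensure adherence to the study protocol".
- Section 2.3: the pilot will estimate recruitment rate, randomisation rate and adherence as separate quantities.

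**The concern.** The decision whether to run the main trial is the chief product of a feasibility pilot, so its rule should give one answer for each possible result. This one does not.

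On a miss, one sentence ends the programme and the next keeps it open. Whoever applies the rule at 18 months must choose between them with the data already in view, which is what a pre-set rule is meant to prevent.

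On a pass, the answer depends on what *recruited* means. Elsewhere the article uses the word for a stage that closes before the embryo-quality filter and before randomisation. A main randomised trial depends on the number who get through that filter. If women who consent but are never randomised count towards the 60, the rule can report success with far fewer than 60 women in the comparison.

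**Working it through.** **The plan's own figures.** The 60-of-100 threshold is stated without derivation, so there is nothing to reproduce. The only computed figure nearby is the margin of ±10.5 points for an 80% interval with 100 women (Section 6.7). The usual formula gives z × √(p(1−p)/n) = 1.2816 × √(0.5 × 0.5/100) = 6.4 points, so that figure does not reproduce. That is a separate matter, and nothing here rests on it.

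**Action on a miss.** No arithmetic is needed.

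| Result at 18 months | Action in Section 6.9 |
|---|---|
| 60 or more recruited | Proceed to the main phase |
| Fewer than 60, first sentence | Stop; no main study |
| Fewer than 60, second sentence | Reassess recruitment strategies, with a larger study still in view |

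The last two rows share one trigger unless *adequate* recruitment in the stop sentence means some number below 60. No such number is given.

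**What the 60 counts.** The order of events is:

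1. Recruitment and consent, from the first consultation to the day of egg collection (Sections 2.6 and 6.7).
2. Day-3 check for three or more good-quality embryos (Section 6.2).
3. Randomisation of those who pass (Section 6.2).

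Let f be the share of recruited women who reach step 3. The article gives no value, so I assume 0.3 to 1.0.

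- If the 60 are recruited women, the number randomised when the rule is just met is 60 × f.
- If the 60 are randomised women, the number of consents needed is 60/f, rounded up. Dividing by 18 gives consents per month.

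| f (assumed) | Randomised if 60 recruited | Consents needed for 60 randomised | Consents per month over 18 months |
|---|---|---|---|
| 0.3 | 18 | 200 | 11.1 |
| 0.5 | 30 | 120 | 6.7 |
| 0.7 | 42 | 86 | 4.8 |
| 0.9 | 54 | 67 | 3.7 |
| 1.0 | 60 | 60 | 3.3 |

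The two readings agree only at f = 1, when every recruited woman passes the day-3 filter.

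**The case against.** The strongest reply concerns the count. The Abstract's 100 are women to be randomised. If Section 6.9 refers to the same 100, the threshold is already 60 randomised and the count is right. That reading is open, so a reader who infers that the rule definitely counts the wrong quantity goes further than the text allows. But Section 6.9 does not adopt that reading, and Sections 2.6 and 6.7 use the word for the earlier stage. The ambiguity stands.

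A reader might also infer that the main trial could start on the recruitment count alone. The article does not support that. Section 6.10 makes continuation depend on data integrity and protocol compliance. Section 7 calls for reassessment if the objectives look unlikely to be met, and Section 2.1 names recruitment, randomisation and adherence as the pilot's objectives. Ethical approval for the main trial is still to be sought. These conditions are real but carry no numbers, and the instruction to proceed in Section 6.9 does not refer to them.

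Two further inferences fail. The absence of an adherence threshold is not an error in itself, because a condensed article may leave it to the full protocol. Nor would planners of the main trial be misled about the randomisation rate, since Section 2.3 has the pilot estimate it separately.

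On the missed target, the two sentences could be read together as no automatic progression, with reassessment before any larger study. The text does not say this, and the first sentence is a plain stop. This part of the reply does not succeed.

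**Conclusion.** The point holds in two parts. First, Section 6.9 contradicts itself on a missed target: stop and reassess are both prescribed for the same result. This needs no assumption. Second, the count behind the go decision is ambiguous between women recruited and women randomised. Taken literally, it can be met with 18 to 60 women randomised for f between 0.3 and 1.0. That range is illustrative because f is assumed; the order of events behind it is stated in the article.

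The defect is confined to the progression decision. It does not alter any participant's treatment or the analysis of outcomes. It should still be corrected before the 18-month decision, because the rule cannot be carried out on a miss and its meaning on a pass is unsettled.

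**What to change.** In Section 6.9:

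1. Define the 60 as women randomised within 18 months.
2. Replace the two sentences on a missed target with one rule in non-overlapping bands. For example: go at 60 or more randomised; reassess from a stated lower bound up to 59; stop below that bound. The sponsor sets the cut-offs.
3. If the sponsor also sets an adherence criterion, state that the worst-performing criterion decides, so that no result falls into two bands. State too whether women in the PGT-A arm with no embryo to biopsy, whom Section 7.3 records as deviations, count as non-adherent.
4. Make the instruction to proceed conditional on the data-integrity and preliminary-results conditions in Sections 6.10 and 7.

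The cost is a few lines of wording. The number randomised is already to be recorded, so no new data are needed. The drawback is a go threshold that is harder to meet: for f below 1, more than 60 consents are required, for example 120 at f = 0.5.

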### 6.10. Data Integrity

We will perform a thorough review of the data collection procedures to ensure adherence to the study protocol and verify the accuracy and completeness of the data. This will include an assessment of missing data, data consistency, and compliance with ethical and regulatory standards. If the data collection processes are found to be compliant with protocol, with minimal missing or inconsistent data, and overall data integrity is upheld, the study will proceed. If significant issues with data integrity are identified, such as widespread missing or inconsistent data, or non-compliance with ethical and regulatory standards, corrective actions will be taken. Persistent issues may lead to study termination if data integrity cannot be assured.

## 7. Preliminary Results

If the preliminary results show promising trends and outcomes consistent with the study hypotheses, and statistical analyses (including Bayesian methods if applicable) indicate the potential for meaningful findings, the study will continue. If the preliminary results are inconclusive or show no evidence of potential benefit, or if analyses indicate that the study objectives are unlikely to be met, the study will be reassessed. Decisions will be made based on the overall value of continuing versus terminating, considering the insights from the preliminary analyses.

To analyse of our outcomes of interest, logistic regression or linear mixed models, as well as survival analyses or chi-square tests, will be used.

### 7.1. Data Monitoring, Quality Control, and Assurance

The Chief Investigator (CI) will be responsible for the ongoing management of the study. The Sponsor will monitor and conduct audits on a selection of studies in their clinical research portfolio. Monitoring and auditing will be conducted in accordance with the UK Policy Framework for Health and Social Care 2017 and in accordance with the Sponsor’s monitoring and audit procedures.

### 7.2. Handling Participants Who Do Not Follow Their Allocated Arm

Participants who do not adhere to their allocated study arm will be tracked through the study’s monitoring system. Reasons for non-compliance will be documented, and alternative approaches will be considered to account for deviations in the final analysis. Non-compliance will also be recorded and assessed to understand its impact on study outcomes. The analysis will include intention-to-treat (ITT) and per-protocol approaches to evaluate the effect of treatment allocation versus the actual received treatment.

### 7.3. Recording and Assessing PGT-A Arm with No Embryos to Biopsy

For participants randomised to the PGT-A arm who have no embryos available for biopsy, detailed documentation will be maintained. This will include the reasons for the absence of viable embryos, such as poor ovarian response or embryo quality issues. These cases will be assessed and recorded as deviations from the intended intervention. The impact of such deviations on the study outcomes will be analysed, and the data will be included in the final study report to provide a comprehensive view of the feasibility and practical challenges of PGT-A’s implementation.

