### 6.4. Embryo Transfer

Only single-euploid embryos or low-mosaic embryos that are deemed suitable to be replaced, with prioritisation based on the morphological grading of the embryos, will be transferred in subsequent frozen–thawed embryo transfer cycles, which could be initiated as early as with the next menstrual cycle following egg collection. Euploid embryos will preferably be transferred to low-mosaic embryos and the couple will need to undergo genetic counselling before transferring a low-mosaic embryo.

The subsequent frozen–thawed embryo transfer (FET) of a single-euploid embryo will occur either in a natural cycle or a hormonally medicated cycle using physiological doses of oestrogen and progestogens to prepare the endometrium.

If patients decide not to transfer mosaic embryos, these instances will be thoroughly documented, including the reasons and clinical factors involved. These data will be incorporated into the study through descriptive analysis, which will outline the frequency of and reasons for these decisions. Additionally, sensitivity analyses will assess how excluding mosaic embryos affects the study outcomes, ensuring that the results accurately reflect both the protocol and real-world practices. The final report will address the implications of transferring versus not transferring mosaic embryos on the study’s primary and secondary endpoints, providing a comprehensive understanding of their impact.

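### Section 7.3 labels PGT-A women with nothing to biopsy as deviations and gives control women no matching rule, which leaves the per-protocol contrast and the adherence outcome open to a one-sided classification

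*Protocol article*

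**What the plan says.** Section 7.3 is written for one arm: "For participants randomised to the PGT-A arm who have no embryos available for biopsy, detailed documentation will be maintained". The reasons it expects are prognostic, "such as poor ovarian response or embryo quality issues", and the classification is explicit: "These cases will be assessed and recorded as deviations from the intended intervention". It then promises follow-through: "The impact of such deviations on the study outcomes will be analysed, and the data will be included in the final study report".

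Section 7.2, on participants who do not follow their allocated arm, says that "alternative approaches will be considered to account for deviations in the final analysis" and adds: "The analysis will include intention-to-treat (ITT) and per-protocol approaches to evaluate the effect of treatment allocation versus the actual received treatment". It does not say who belongs to the per-protocol set.

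Other sections bear on the point:
- Section 6.2 randomises on day 3, in women with at least three good-quality embryos.
- Section 6.3 has biopsy done on those embryos in the PGT-A arm that become blastocysts. Control women go to a fresh transfer on day 5, or to a frozen one where indicated.
- Section 4 makes adherence part of the primary outcome.
- Section 5 lists clinical pregnancy per randomised woman as a secondary outcome.
- Section 6.4 adds, for mosaic embryos, that "sensitivity analyses will assess how excluding mosaic embryos affects the study outcomes".

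**The concern.** Blastocyst status becomes known only after randomisation, and in both arms some women may have no blastocyst. Having none is an early result of the cycle and a marker of poor prognosis. It is not a choice by the couple or the clinic to depart from allocation. Section 7.3 nevertheless files it as a deviation, for the PGT-A arm only.

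Two analyses could pick up that label. A per-protocol analysis by treatment actually received would naturally leave out a woman who was never biopsied, while a control woman in the same position carries no label and may stay in as a failure. The arms would then differ in prognosis by construction. An adherence rate built from recorded deviations would also fall although nobody departed from allocation. Both matter beyond the pilot, because Section 2.1 intends the pilot data to enter the main trial and Section 7 lets promising trends inform continuation.

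The mosaic sensitivity analysis has a related asymmetry. Only PGT-A embryos are tested, so mosaics can be identified and removed in one arm only.

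**Working it through.** The plan gives no figure on this point, so there is none to reproduce. The check is a reading of the sections followed by an illustration on assumed rates.

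**1. Is the woman a deviation under the plan's own pathway?** Section 6.3 makes biopsy conditional on an embryo becoming a blastocyst. A PGT-A woman with no blastocyst has therefore received what that section describes, and the Section 7.3 label does not fit it. Control women also depend on development after day 3, and no section classifies those with nothing to transfer.

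**2. Size of the per-protocol shift if exclusion is one-sided.** Inputs, all assumed:
- q = share of randomised women with no blastocyst, equal in both arms
- p = pregnancy rate in the remaining women, equal in both arms (no treatment effect)
- pregnancy rate of 0 in women with no blastocyst

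Intention-to-treat rate in each arm = (1 − q) × p. If these women are excluded in the PGT-A arm and kept in control:
- PGT-A per-protocol rate = p
- control per-protocol rate = (1 − q) × p
- spurious difference = p − (1 − q) × p = q × p
- spurious risk ratio = 1 / (1 − q)

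| q | p | Control | PGT-A | Difference (points) | Ratio |
|---|---|---|---|---|---|
| 2% | 30% | 29.4% | 30.0% | 0.6 | 1.02 |
| 5% | 40% | 38.0% | 40.0% | 2.0 | 1.05 |
| 10% | 33.3% | 30.0% | 33.3% | 3.3 | 1.11 |
| 10% | 40% | 36.0% | 40.0% | 4.0 | 1.11 |
| 20% | 40% | 32.0% | 40.0% | 8.0 | 1.25 |
| 20% | 50% | 40.0% | 50.0% | 10.0 | 1.25 |

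If both arms exclude these women, both rates are p. If both keep them, both are (1 − q) × p. Either way the spurious difference is 0. If women with no blastocyst conceive at some rate r above 0, the difference is q × (p − r), so q × p is the upper value.

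**3. How large might q be?** Section 6.2 requires at least three good day-3 embryos. If k embryos each become a blastocyst independently with assumed probability b, the chance of none is (1 − b)^k. For k = 3 this is 0.34 at b = 0.3, 0.125 at b = 0.5 and 0.064 at b = 0.6. For k = 6 it is 0.118, 0.016 and 0.004. The gate may therefore keep q low, but does not remove it.

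**4. Adherence, if these cases count as non-adherence.** With 100 women at 1:1 (Sections 6.7 and 2.8) there are 50 per arm. PGT-A-arm adherence is at most 1 − q. For q = 2% to 20% that is 98% down to 80%, or 1 to 10 women. Overall adherence is at most 1 − q/2, or 99% down to 90%.

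**5. Scale against noise.** At 30% and 50 women per arm, the standard error of a difference is √(2 × 0.30 × 0.70 / 50) = 0.092. A shift of 3.3 points is 3.3 / 9.2, about a third of one standard error.

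**The case against.** The strongest reply is that the harm depends on steps the article does not take. A reader might infer that the per-protocol analysis drops these women from the PGT-A arm alone, that adherence is thereby understated, and that the progression decision is misled. The text does not establish any of the three.

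- The per-protocol set is undefined, and Section 7.3 does not mention it. Its membership may be settled in the full protocol or the analysis plan.
- Section 7.2 is worded neutrally between arms, so a control woman with no transfer might be excluded too. The bias needs exclusion in one arm and retention in the other.
- Section 7.3 does not call these cases non-adherence. How often PGT-A cannot be delivered is proper feasibility information.
- The only numeric progression threshold is recruitment, 60 of 100 women in 18 months (Section 6.9). No adherence threshold exists to be missed.

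The rates are also assumed, the shift is small against the pilot's noise, and intention-to-treat is planned. On mosaics, Section 6.4 gives no denominator, and the Abstract and Discussion treat mosaic outcomes as not yet known. They cannot be called likely failures.

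All of this stands against the stronger reading. What it does not answer is the rule that the article does state. The label covers one arm, it does not fit the pathway in Section 6.3, and Section 7.2 uses the same term when it speaks of accounting for deviations in the final analysis. That is a rule badly fixed, not a detail left out.

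**Conclusion.** The point holds in conditional form. Section 7.3 classifies a prognostic event after randomisation as a deviation in the PGT-A arm only, and control has no counterpart.

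If that label leads to exclusion in one arm, the per-protocol contrast is biased toward PGT-A by q × p. This is about 3.3 points at assumed q = 10% and p = 33%, and 0.6 to 10.0 points over q = 2–20% and p = 30–50%. These figures assume equal q in both arms, no treatment effect, and no pregnancies without a blastocyst. If the label is read as non-adherence, PGT-A-arm adherence falls by q. Whether either happens is not stated.

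Intention-to-treat results and pregnancy per randomised woman are not affected. The weight is moderate: no primary comparison is invalid, but the rule should be put right before analysis.

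**What to change.** Reword Section 7.3 to say that having no blastocyst, or no transferable embryo, is an outcome of the allocated strategy in both arms. Record and report it in both arms, separately from non-adherence. Keep these women in the denominator of the intention-to-treat and the per-protocol analyses. In Section 7.2, limit per-protocol exclusions to true departures from allocation, defined alike in both arms.

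In Section 6.4, run the mosaic sensitivity analysis at woman level with all randomised women in the denominator. If one version counts a mosaic transfer as no pregnancy, label it a worst-case bound, because it can recode real pregnancies as failures in the PGT-A arm only.

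The cost is protocol wording, plus recording the same event in control women. The downside is a possibly less favourable per-protocol estimate for PGT-A. The feasibility information that Section 7.3 seeks is kept, since the frequency of these cases is still reported.
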